### Supplementary Feedback on User Experience

In addition to questions on the primary and secondary outcomes associated with the randomized controlled trial, participants in the intervention group will be asked a set of 12 additional questions on their experience using the *Minder* app at the end of the 30-day follow-up assessment. These questions will be used to inform the ongoing development of the app and use a combination of Likert-type and open text box responses to collect information on experiences using specific app components, reasons for using (or not using) features such as the Peer Coach, and any suggestions for improving key features such as the *Minder* chatbot.

### Sample Size and Power

The sample size calculation for a small effect assessed by the PHQ-9, GAD-7, and USAUDIT-C was calculated using an effect size defined by Cohen *d*=Δ/σ, where Δ is the group mean difference at the completion of the study and σ is the (pooled) within-group SD. For a small effect size (Cohen *d*=0.2), the sample size required to have 80% power at the level of significance *P*=.02 (0.05/3 primary outcomes) is 524 in each group. Assuming a 30% attrition rate, we require 748 participants in each group. To account for a conservative estimate of a small effect size and a 30% attrition rate, we estimate that a minimum of 748 randomized participants will be needed for each study group, totaling at least 1496 participants.

### Sample Recruitment

Sample recruitment will use a widespread, multifaceted approach that includes web-based and offline interactions with students as well as university faculty and administrators.

Web-based recruitment will occur through social media engagement via Facebook, Instagram, Twitter, and Reddit research laboratory or project pages or through recruitment material reposted by organizations represented on the SAC or UBC-affiliated groups (eg, student clubs and student government representatives). Web-based recruitment will also occur through the linked Student e-Mental Health survey, a version of the World Mental Health International College Student survey adapted for Canadian contexts and administered at UBC (approved by the UBC Behavioral Research Ethics Board under ethics ID #H19-02538 [34]). At the end of the linked survey, prospective participants will receive a message offering an opportunity to test a mental health and substance use app, and interested students will be redirected to a registration form for this study where they can consent and register to participate if qualified.

Offline recruitment will include in-person booths of student team members in frequented communal areas with high student traffic (eg, student union and main campus lawn or pathway) around the UBC Vancouver campus; placing recruitment posters in public places on campus; and distributing mini posters with QR codes to classes, students, and student groups on campus.

Student engagement will also occur through collaboration with select UBC faculty members and administrators. Specifically, members of the research team will attend in-person and web-based courses at the university to provide students with a short presentation about the study and will request that recruitment materials be included on course web pages and emails. In addition, student groups at the university will be contacted to share recruitment information with their members through emails and newsletters or to coordinate with study team members attending group meetings or events to directly share information about the study. Invitations to participate in this study will also be sent to students who have previously expressed interest in participating in research studies and asked to be contacted if study opportunities with the research laboratory became available.

Widespread signage will also be implemented through posters at on-campus bus stops and digital screens in on-campus buildings, as well as printed posters within buses designated for routes with direct connections to the university.

### Randomization and Study Arms

A study participant is defined as an individual who has completed the baseline survey and has been randomly assigned into either the control or intervention group. Participants are randomized using a stratified block randomization function built into the app. The randomization list for the built-in function was created using the web-based stratified block randomization list creator in the clinical trial software Sealed Envelope (Clerkenwell Workshop) [35]. To ensure that each arm of the randomized trial contains an equal number of participants endorsing a history of substance use, participants will be assigned to either group A (substance use: any medical opioid use, nonmedical opioid use, or nonmedical stimulant use) or group B (nonsubstance use), based on their answers to the opioid and stimulant use questions in the baseline survey. After being stratified into group A or group B, individuals are then automatically randomly assigned (via the randomization list embedded into the app) to either the control or intervention arm of the trial using a 1:1 ratio in blocks of 10.

Those randomized into the control group will receive a message saying that they will be asked to complete an additional survey at 30 days and will only receive full access to the app after that. During the 30-day study period, the control group participants will receive a restricted version of the app that only permits access to the following: an introduction video with several students providing a broad overview of the different aspects of the app and its potential value, several onboarding slides with a short summary of the main app components, and baseline and follow-up assessment surveys plus reminder notifications to complete those surveys. Participants randomized into the intervention group will receive immediate access to the full *Minder* app.

### Strategies to Improve Adherence to Intervention Protocols

All participants will receive both email reminders and in-app push notifications to complete the assessment surveys. More specifically, after the initial email to prospective participants with instructions to download the app and complete the baseline survey (to be randomized), an email reminder to complete the baseline survey will be sent on day 7 and again on day 20 to those who have not yet completed it. Participants who have not completed the baseline after 1 month may receive an additional email reminder. Participants assigned to the intervention group will then receive an email and push notification to complete the 2-week survey. Participants in both the intervention and control groups will receive an email and push notification 30 days after baseline completion and a group assignment to notify them to complete the follow-up survey, along with a reminder email 5 days and 11 days later if the survey has still not been completed.

Participants in the intervention group will also receive general in-app push notifications on days 4, 18, and 24 to highlight the different features of the app. The intervention group also receives a push notification when they have a new in-app message from their assigned Peer Coach, either a scheduled message (at assignment and around the study midpoint) or a reply to an ongoing text conversation with the participant.

### Data Management and Withdrawal

All data are collected in the app and stored on secure servers located in Canada. The research team will download all study data regularly (business days excluding statutory holidays) and monitor for any issues with data collection. Access to the data will be limited to the members of the research team. To ensure that participant information and privacy are protected, the *Minder* app backend will abide by the UBC Research Ethics Board guidelines and British Columbia’s Freedom of Information and Protection of Privacy Act. Participant data are collected using a unique study ID value within the system to ensure that survey response data and app use data remain separate from identifying information contained in the participant registration and remuneration documentation. The only exception will be if a participant elects to withdraw from the study and indicates their decision to have their data deleted; in this case, the data manager will use the unique study ID value to link their registration information with their survey response data and app use data and delete all their data from the system and all saved files.

### Data Analysis Plan

#### Statistical Analysis

The primary analysis will be intention to treat (ITT) to estimate the causal effects of the assignment to treatment on the trial outcomes for all participants. A participant within the study is defined as an individual who has completed the baseline assessment survey and has been randomized into either the control or intervention group. The analysis will consider the following 2 features of the trial design: 3 primary end points and the method of randomization. The effects of some of these design features (ie, randomized blocks) are expected to be small and statistically nonsignificant. Nonetheless, we will use multilevel regression and SAS (version 9.4; SAS Institute Inc) and R (version 4.3.1; R Foundation for Statistical Computing) software in our analyses to control for these effects.

Before any testing, we will compare the baseline differences between the randomization groups on demographic (eg, sex, gender, and ethnicity), socioeconomic (eg, year of study), and personal risk variables (eg, mental health diagnoses and use of mental health treatments). Any baseline prognostic variable with a standardized difference between the groups of Cohen *d*>.05 will be considered a candidate variable to control for in the analysis. The selection of Cohen *d*>.05 is arbitrary: there is no accepted threshold to determine a meaningful difference between the 2 groups. However, this is a very small effect and indicates approximately a 4% nonoverlap between the 2 populations.

For the 3 primary end points (PHQ-9, GAD-7, and USAUDIT-C), a global test with the null hypothesis of no treatment difference in all primary end points between the control and treatment groups will be conducted using a marginal multivariate regression model for correlated data on PHQ-9, GAD-7, and USAUDIT-C. Compared with testing each outcome separately, the advantages of the global test from joint modeling include more parsimonious hypothesis tests and mitigated concern of multiple testing issues [36-38] as well as pooling of the information over the correlated outcomes to increase study power, especially with missing outcomes [39]. When the global test rejects the null hypothesis and we conclude that there is an intervention effect on at least 1 of the 3 end points, we will then analyze each end point separately to identify which of the 3 study end points are affected by the intervention. We will use the sequential Hochberg correction method [40] to control the overall family-wise error rate at α=.05 when testing the hypothesis for each individual primary end point.

The general approach for analyzing all the types of study outcomes separately (including the 3 primary end points and the secondary end points) will be the generalized linear mixed-effect models (GLMMs) for clustered measures, with the randomization block as the clustering variable. These models can handle a wide range of outcome types, including continuous, binary, ordinal, and count, and can account for the correlations among observations within the same cluster. Specifically, we will analyze each primary end point using a linear mixed-effect model, a special case of the GLMM. For secondary outcomes, we will use linear mixed-effect models to analyze mental well-being measures and readiness to change measures, mixed logit models to analyze the connection to services and support-related measures (binary: yes or no), mixed-effects quasi-Poisson regression models with the log link (a special case of GLMMs) for substance use frequency measures, and mixed-effects proportional odds ordinal logistic regression (another special case of GLMMs) for self-efficacy measures. The treatment effect on an outcome at 30 days will be assessed using a GLMM with the treatment allocation as the main explanatory variable and with adjustment for baseline outcome assessment value and other baseline prognostic factors as fixed effects and the randomization block as a random effect. By properly specifying the GLMM, a wide range of scientific hypotheses can be tested, including the primary ones regarding treatment effect estimation. The quality of statistical inferences will be substantiated through rigorous model checking and validation techniques. When statistical models assume that residuals at certain levels follow normal distributions, this assumption will be checked using a normal probability plot, in which the ranked residuals are plotted against corresponding points on a normal distribution curve. When substantial departures from the normal residual assumption are found, robust empirical SE estimates that are valid with nonnormal residuals will be used for statistical inference. We will use SAS software (version 9.4; SAS Institute Inc) and R (version 4.3.1; R Foundation for Statistical Computing) for the statistical analyses of our primary and secondary outcomes. Subgroup analysis will be performed using the GLMM on the subsets of data formed by the subgroup.

Missing data will take two forms: (1) missed questions or items and (2) unit nonresponse or attrition (withdrawals and lost to follow-up). We anticipate that most missing data are owing to attrition, which leads to unit nonresponse at the 30-day assessment. To reduce bias and avoid the loss of statistical power in our analysis of primary and secondary outcomes, we will use likelihood-based direct estimation, which is equivalent to performing multiple imputations under the model to predict values for missing data. One advantage of using the abovementioned multilevel GLMMs for analyzing primary and secondary outcomes is that it uses all the available data by including those study units with missing outcome values and it produces valid inference under the assumption of missing at random, which is a more relaxed assumption of missing data mechanism than missing completely at random. The missing values will be regarded as missing at random when the nonresponse behavior is believed to be a function of observed data, particularly common when assessing mental health and substance use behaviors and using a digital self-report format. The potential bias of these inferences will be quantified if these missing data were suspected to be nonrandom even after conditioning on the observed data, using the methods [41,42] developed by our team member and implemented in R package *isni* [43]. In summary, state-of-the-art statistical methods will be used to address these missing data issues.

In addition to the primary analysis using ITT, we will conduct a secondary analysis to evaluate the Complier Average Causal Effect (CACE) of the intervention. The primary analysis using ITT estimates the causal effects of treatment assignment on the trial outcomes for all participants, regardless of whether those assigned to the intervention actually use the *Minder* app (ie, complying with the treatment assignment). The results from the ITT analysis will be useful to policy makers and inform the effects of applying the treatment program to the population. Although ITT analysis is informative and valid, one limitation of the ITT analysis is that it estimates the program effectiveness rather than method efficacy. The program effectiveness depends on the proportion of compliers, which can change (eg, students change their willingness to use the intervention after they learn that the intervention works). Thus, to complement this approach, we will also conduct a CACE analysis that will focus on the intervention efficacy of those who actually use the e-intervention. The CACE analysis in conjunction with the abovementioned ITT analysis will provide a more complete picture of the intervention effect. By identifying who uses and benefits from the intervention, the trial can yield findings of direct interest to the scientific community and individual students. To overcome the challenge that the study participants’ compliance and app use behaviors are self-selected in nature and not randomized, we will use the principal stratification approach to estimate the CACE effects on multiple end points in RCTs with treatment noncompliance [36] and the dose-response relationship between the extent of app use (eg, completed Chatbot Activities and number of contacts with Peer Coach) and intervention effect [44]. Given the diverse nature of the target population combined with the self-guided use of intervention components, we also plan to examine heterogeneity in treatment effects using a series of exploratory analyses that use sociodemographic (eg, gender and year of study) and assessment data (eg, symptom level on PHQ-9 and GAD-7) collected at baseline to examine the impact of the *Minder* app on key subgroups.

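### Covariates beyond the baseline outcome are screened on observed baseline imbalance (d>.05), so chance rather than prognostic strength largely decides the adjustment set; the cost is modest and the test errs on the conservative side

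*Protocol article*

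**What the plan says.** All of this is in the Statistical Analysis section of the protocol article.

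- **Timing and basis of the screen.** "Before any testing, we will compare the baseline differences between the randomization groups on demographic", socioeconomic and personal risk variables.
- **The rule.** "Any baseline prognostic variable with a standardized difference between the groups of Cohen" d ">.05 will be considered a candidate variable to control for in the analysis".
- **Its justification.** The authors call the cut-off arbitrary and defend it by its size: "this is a very small effect and indicates approximately a 4% nonoverlap between the 2 populations".
- **The outcome model.** The treatment effect at 30 days comes from a mixed model "with adjustment for baseline outcome assessment value and other baseline prognostic factors as fixed effects", with the randomisation block as a random effect. The baseline value of the outcome is always in the model. The other factors are not named, and the d>.05 screen is the only route to choosing them that the article gives.

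**The concern.** In a correctly randomised trial, a baseline difference between arms is chance by design. A covariate improves precision in proportion to how well it predicts the outcome, whether or not it happens to be imbalanced. A screen on observed imbalance therefore picks covariates on the wrong property. It drops good predictors that happen to be balanced and admits others through noise.

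The screen also affects the standard error. The covariates left out are exactly those whose arm difference turned out small, so they disturb the treatment estimate less than usual. The model's standard error ignores that selection and charges their full variance. The reported error is then larger than the true sampling variability.

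At stake are some precision on the three primary end points and a primary model whose covariates are known before the arms are compared.

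**Working it through.** **Inputs from the protocol article.** Cut-off d>.05 (Statistical Analysis). From Sample Size and Power: d=0.2, 80% power, alpha 0.05/3 = 0.0167, 524 per arm before attrition, and "Assuming a 30% attrition rate, we require 748 participants in each group".

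**Assumptions.**
- The cut-off is read as |d|>.05, since the sign of a baseline difference is arbitrary.
- The article does not give the share of outcome variance that the selectable covariates explain. Shares of 5%, 10% and 20% are used, spread equally over six independent covariates.
- Every variable passing the cut-off is adjusted for.

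**1. The plan's own figures.**
- n = 2(z₁₋α/₂ + z₀.₈)²/d² = 2(2.394 + 0.842)²/0.04 = 523.5, so 524 per arm, matching "0.05/3 primary outcomes) is 524 in each group" with a two-sided test.
- 524/0.7 = 748.6, which the article gives as 748.
- The 4% nonoverlap also reproduces: Cohen's U1 at d=.05 is 3.9%. It describes the size of the difference, not how often chance produces one that large.

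**2. Chance imbalance.** SE(d) = sqrt(2/n), and P(|d|>.05) = 2[1 − Φ(.05/SE)].

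| n per arm | SE(d) | .05 in SEs | P(pass) per variable | P(at least one of six passes) |
|---|---|---|---|---|
| 748 | 0.0517 | 0.97 | 33% | 1 − 0.666⁶ = 91% |
| 524 | 0.0618 | 0.81 | 42% | 1 − 0.582⁶ = 96% |

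At 748 per arm, about two thirds of useful predictors are left out in any one trial.

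**3. Why the standard error is too large.** Take 748 per arm with no attrition and a 20% share.
- The variance of an excluded variable's difference, given |d|≤.05, is 1 − 2cφ(c)/(2Φ(c) − 1) of its usual value. With c=0.967 this is 0.275.
- True SD ≈ 0.0517 × sqrt(0.80 + 0.20 × 0.666 × 0.275) = 0.047.
- Reported SE ≈ 0.0517 × sqrt(1 − 0.334 × 0.20) = 0.050, about 5% too large.
- Simulation gives 0.0474 and 0.0499.

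**4. Consequence under the planned design.** Large-sample simulation: screen at 748 randomised per arm, outcome analysed in 524 per arm, alpha 0.0167, d=0.2, SD after baseline adjustment taken as 1. Power with no extra adjustment is 80%.

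| Assumed share | Reported SE / true SD under rule | Excess | Type I error under rule (nominal 1.67%) | Power, rule | Power, prespecified set |
|---|---|---|---|---|---|
| 5% | 0.0613 / 0.0607 | 1% | 1.6% | 81.0% | 82.4% |
| 10% | 0.0607 / 0.0597 | 2% | 1.5% | 81.9% | 84.5% |
| 20% | 0.0597 / 0.0574 | 4% | 1.3% | 84.0% | 89.0% |

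The prespecified column can be checked by hand. At 10%, SE = 0.0618 × sqrt(0.9) = 0.0586, and Φ(0.2/0.0586 − 2.394) = 0.846.

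**5. Sensitivity to the baseline outcome.** Suppose the baseline value of the outcome explains 36% of total variance (also an assumption), with the shares again taken of total variance. Power at d=0.2 is then about 96% under the rule against 97% (5% share), 96.5% against 97.8% (10%), and 97.7% against 99.3% (20%). The loss is about 1 to 2 points. The reported SE is about 1.5%, 3% and 6% too large.

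**The case against.** Several points on the other side stand and limit the finding.

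- **The screen does not use outcomes.** It involves baseline variables only and precedes any test. The Masking and Continued Monitoring sections have a blinded statistician working from a blinded database, and |d| does not change if the arm labels are swapped. A reader might infer that covariates can be picked to favour a result. The article does not support that.
- **The strongest predictor is outside the rule.** The baseline value of each outcome is always adjusted for.
- **The text says only candidate.** Passing the cut-off may not mean automatic inclusion, and a statistical analysis plan not shown may hold the final list. Automatic inclusion, as simulated, is one reading. An unstated last step would add discretion, but the pool would still be filtered by chance imbalance.
- **The low cut-off is not the defect.** A lower threshold lets more covariates in and so loses less than a higher one would.

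Two stronger readings are tempting. The first is that the rule produces invalid or falsely significant primary results; the error runs the other way, with type I error below nominal. The second is a large power loss, above ten percentage points. That needs an effect well below the planned d=0.2, such as 0.13 SD, together with a generous covariate share and a substantial baseline contribution. The article gives no basis for that combination.

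**Conclusion.** The point holds as a modest efficiency and prespecification weakness. The chance-selection figure, 33% per variable at 748 per arm and 42% at 524, rests only on the article's own numbers and on reading the cut-off as an absolute difference.

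The consequences depend on the unknown variance share. For shares of 5% to 20% at the planned d=0.2, prespecified adjustment would gain about 1 to 5 percentage points of power, or about 1 to 2 if baseline explains 36% of variance. In every case examined the rule does better than no extra adjustment, and power does not fall below the planned 80%. What is given up is available precision and a primary model fixed in advance, in return for no inferential benefit over a fixed set.

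**What to change.** Delete the d>.05 rule from the Statistical Analysis section. Before unblinding, name one covariate set for the primary models, chosen by expected prognostic strength from data already collected:

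- the baseline value of the outcome;
- the opioid/stimulant randomisation stratum;
- a short list from the variables the section already mentions, such as gender, year of study, mental health diagnoses and treatment use.

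Adjust for this set whatever imbalance is observed, and report baseline differences descriptively only. The short list is the trial team's choice; what matters is that it is fixed and does not depend on observed imbalance. If a separate analysis plan already names the covariates, point to it and drop the rule.

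The cost is one paragraph of wording, with no new data, no change to recruitment and no change to the sample size.

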*Minder* delivers a suite of evidence-based interventions that have been tailored to help university students improve their well-being and manage their substance use through 4 main components: Chatbot Activities, Services, Community, and Peer Coaching (Figure 2). The Chatbot Activities consist of an automated preprogrammed chatbot text and videos that draw primarily from cognitive behavioral therapy (CBT), given its demonstrated transdiagnostic efficacy in web-based intervention programs [21-24]. The Chatbot Activities also incorporate evidence-based content derived from metacognitive therapy, dialectical behavioral therapy, and motivational interviewing. These activities have been developed through collaboration with mental health professionals and university students so that the information can be presented in a way that is consistent with evidence-based practices and appropriate for this demographic. The Chatbot Activities were designed to support students on a range of topics and include content to manage mild to moderate distress and emotions and to help navigate general student life (eg, relationships, time management, and sleep hygiene). In addition, the content of the Chatbot Activities relates to the use of alcohol, cannabis, opioids, and stimulants, including general psychoeducation and motivational interviewing. These topics encapsulate many general skills included in CBT for managing emotions (eg, recognizing automatic thoughts) as well as additional topics highlighted by students through our codevelopment process as being more relevant to student well-being, such as transitioning to university. To increase the accessibility of the app, all activities that include video content have been closed-captioned in both English and French. Users have access to this entire range of content in the app and can choose to engage with any activities, regardless of their current mental health or substance use status. The Services component of *Minder* includes a validated psychosocial screening tool that provides users with tailored recommendations and resources based on their current needs and preferences [25]. It consists of a short survey with several categories (mental health, safety, substance use, abuse, housing, education, and sexual wellness) and an individually tailored list of relevant services that can be filtered by factors such as cost, availability, and delivery method. The Community component of *Minder* contains a searchable inventory of student groups or clubs at the university, which can be filtered according to the student’s interest. Finally, to support the use of the app, Peer Coaches (university student volunteers that have been trained by the research team’s clinicians) are available to help users navigate through different app components and provide nonclinical peer support. Once a Peer Coach is assigned, users can communicate with their coach through secure in-app texting or video calls in a synchronous or asynchronous manner. In this study, users in the intervention group will be offered Peer Coaches who will reach out to their assigned users twice during the study period (ie, at the beginning of the trial upon assignment and around the midpoint of the trial). Additional information on the development of *Minder* and its components can be found in the study by Vereschagin et al [14].

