### Limitations

Although many similar e-interventions have experienced large loss to follow-up and poor participant engagement, the incorporation of Peer Coaches for each participant in addition to well-spaced reminders to return to the app and complete baseline and follow-up surveys are expected to improve app engagement and reduce loss to follow-up. It is also important to note that this intervention was designed for use in the general population with mild symptomology so recruitment may be challenging as these students may be less interested than a clinical population in participating in a mental health study. We have addressed this challenge by using a comprehensive set of recruitment methods to engage potential participants in the broader university population. The intervention also includes components relevant to all students, including content addressing general well-being and more clinically relevant content. Students who choose to participate in this study may also be more motivated than the general population to seek help or to improve their mental health or substance use concerns. This may impact their willingness to participate and responses to self-report surveys, which may lead to reporting bias; however, we believe that these biases will not differ across the surveys or between intervention and control groups. Moreover, mental health and substance use concerns are high among university populations, with a large fraction experiencing psychological distress; therefore, a study sample reporting a range—including elevated levels—of mental health or substance use concerns is representative of students’ functioning, which supports the generalizability of the results to the broader student population. In addition, participants in the intervention group will be unblinded, which could lead to biased self-reports of mental health symptomology related to placebo effects and social desirability. Although our use of standardized assessments completed via nonidentifiable web-based surveys should help mitigate some of these risks, it will be important to address this limitation in future studies on the *Minder* app by incorporating a sham or placebo control in future trials and examining the cognitive mechanisms associated with targeted outcomes.

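### The models cluster only on randomisation block, so if outcomes vary by Peer Coach in the intervention arm, the standard errors will be too small for inference beyond the coaches used

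*Protocol article*

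**What the plan says.** Statistical Analysis (Data Analysis Plan) names two design features that the analysis will take into account: the three primary end points and the way participants were randomised. It expects block effects to be small but models them anyway. The separate outcome models are "generalized linear mixed-effect models (GLMMs) for clustered measures, with the randomization block as the clustering variable", and the block is their only random effect. A global test from a marginal multivariate model comes first and decides whether the end points are tested separately. Robust standard errors are a fallback for non-normal residuals; clustering by coach is not mentioned.

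Under Intervention, "users in the intervention group will be offered Peer Coaches who will reach out to their assigned users twice during the study period", and an assigned coach can then be reached by text or video. Limitations refers to "the incorporation of Peer Coaches for each participant". Under Randomization and Study Arms, controls have a restricted app without coaching, and allocation is made "using a 1:1 ratio in blocks of 10". Coach contact enters the analysis only as a measure of dose in a secondary analysis. Sample Size and Power treats participants as independent.

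**The concern.** The design is partially nested: participants are randomised individually, but in one arm only they are then grouped under the people who deliver part of the intervention. If coaches differ in responsiveness or persistence, and this affects symptoms or drinking, users of the same coach will have correlated outcomes.

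The block effect cannot stand in for this. Each block of 10 contains both arms, so a block effect shifts both sides of the comparison together and largely cancels, whereas a coach effect touches only the intervention mean. Nothing in the article ties coaches to blocks.

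At stake is the stated precision of the three primary treatment effects when they are read as what the programme would do with other coaches. The plan's own reasoning favours checking: it models a block effect that it expects to be negligible and leaves out a grouping with a more direct route to the outcome.

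**Working it through.** **Inputs from the article (Sample Size and Power).** "For a small effect size (Cohen *d*=0.2"), 80% power, and "0.05/3 primary outcomes) is 524 in each group"; then "Assuming a 30% attrition rate, we require 748 participants in each group".

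**Reproducing the plan's figure.** Two-sided α = 0.05/3 = 0.0167, so z = 2.394; for 80% power z = 0.842.

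n = 2 × (2.394 + 0.842)² / 0.2² ≈ 523.5, rounded up to 524 per arm, which matches.

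Dividing the unrounded 523.5 by 0.7 gives 747.8, hence 748 (dividing the rounded 524 by 0.7 gives 748.6). Both figures assume independent participants.

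**Assumed, because the article does not give them.** Users per coach among those analysed, m = 10 or 20 (about 52 or 26 coaches for 524), with 50 as a stress case; coach ICC of 0, 0.01 or 0.02, with 0.05 as a stress case. Total variance is set to 1 in both arms.

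**Formulas.**
- Design effect in the intervention arm: DE = 1 + (m − 1) × ICC. In the control arm it is 1.
- True SE divided by block-only SE, with no block variance: √((1 + DE)/2).
- Actual coverage of a nominal 95% interval: 2Φ(1.96/ratio) − 1.
- Power at d = 0.2 with the correct SE: Φ(0.2/√((1 + DE)/524) − 2.394).

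**Worked line, m = 20 and ICC = 0.02.** DE = 1 + 19 × 0.02 = 1.38. Ratio = √(2.38/2) = 1.091. Coverage = 2Φ(1.96/1.091) − 1 = 92.8%. SE = √(2.38/524) = 0.0674, so power = Φ(2.968 − 2.394) = 0.72.

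| Users per coach | ICC | DE | SE ratio | Coverage | Power |
|---|---|---|---|---|---|
| any | 0 | 1.00 | 1.000 | 95.0% | 0.80 |
| 10 | 0.01 | 1.09 | 1.022 | 94.5% | 0.78 |
| 10 | 0.02 | 1.18 | 1.044 | 94.0% | 0.76 |
| 20 | 0.01 | 1.19 | 1.046 | 93.9% | 0.76 |
| 20 | 0.02 | 1.38 | 1.091 | 92.8% | 0.72 |
| 50 (stress) | 0.05 | 3.45 | 1.492 | 81.1% | 0.41 |

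**Check by simulation.** Coach effects were placed in the intervention arm only, with zero block variance and 4,000 replicates. At m = 26 and ICC = 0.02 the simulated SE ratio was 1.12; the formula gives √((1 + 1.50)/2) = 1.118.

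**The case against.** Four counter-arguments deserve weight.

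- **Caseload and ICC are unknown.** A reader might infer that the intervals are too narrow. The article does not support that: several users per coach is an inference from its plural wording about assigned users and from the numbers involved, and no ICC is given.
- **Coaching is a modest part of the programme.** It is offered, nonclinical and limited to two scheduled contacts, alongside an automated chatbot, a service finder and a club directory. Under intention to treat, users who ignore their coach dilute the correlation. As an illustration on assumed figures, an ICC of 0.05 among engaged users with 30% engagement gives 0.3² × 0.05 = 0.0045 overall. At 524/30 ≈ 17.5 users per coach, DE = 1 + 16.5 × 0.0045 ≈ 1.07 and the SE rises by about 2%.
- **Type I error.** A reader might infer that the primary tests are too liberal. That needs a particular null, in which some coaches help and others harm and the average is exactly zero. If the intervention affects nobody, coaches cannot differ, the ICC is 0 and the tests keep their size.
- **Target of inference.** For the effect averaged over the coaches actually used, differences between coaches already sit in the intervention-arm residual variance. The extra variance is needed only to generalise to other coaches.

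All four stand, and they limit the size and scope of the point. They do not remove the omission, which is fixed in the text: the clustering variable is named, and it is not the coach. Generalising is also a natural aim here, since the article says the intention-to-treat results should inform policy makers about applying the programme to the population.

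**Conclusion.** The point holds conditionally. The stated models cannot reflect variation between coaches, and if there is any, the standard errors are too small for inference beyond these volunteers. On 524 analysed per arm and 10 to 20 users per coach, the true SE is unchanged at ICC 0 and about 2% to 9% above the reported SE at ICC 0.01 to 0.02. The consequence is mainly for interval coverage. The stress row shows that a large effect would need big caseloads together with strong coach effects across the whole arm, and nothing in the article points to that.

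It would go too far to say that the results apply only to these volunteers: three of the four app components involve no coach. Nor does the point call for a new sample size. It is a low-cost improvement to the analysis, and it would let the trial measure a quantity that the present plan leaves unknown.

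**What to change.** Retain the ID of the assigned coach for each intervention participant, and prespecify a sensitivity analysis by assignment, whether or not the user replied:

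- **Each primary end point:** the planned mixed model plus a coach random effect in the intervention arm only, with controls as singletons and arm-specific residual variance.
- **Global test:** coach-clustered robust standard errors, because a random effect does not fit directly into a marginal model.
- **Reporting:** give the coach ICC, and qualify any primary conclusion that does not survive.

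Coach ID reveals the arm, and giving controls singleton dummy IDs would not hide it, because the intervention clusters would stand out. To respect Masking and Continued Monitoring, run this after the blinded primary analysis is locked, or have the data manager run it from code written beforehand.

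The cost is one extra analysis after lock, with slightly wider intervals if coaches differ. The app presumably already holds the coach ID in order to route messages, so no new data collection should be needed.
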